#### **4.5.2 Adverse Event Grading Criteria**

Local adverse events, systemic adverse events, vital signs, and laboratory testing parameters after vaccination were determined based on the *Guiding Principles of Adverse Events Grading Criteria for Clinical Trials of Prophylactic Vaccines*.

**Table 3 Local Adverse Events Grading Table**

| Symptoms/signs               | Grade 1                                                                                              | Grade 2                                                                               | Grade 3                                                                                                                                                              | Grade 4                                                         |
|------------------------------|------------------------------------------------------------------------------------------------------|---------------------------------------------------------------------------------------|----------------------------------------------------------------------------------------------------------------------------------------------------------------------|-----------------------------------------------------------------|
| Pain                         | Do not or slightly affect physical activities                                                        | Affect physical activities                                                            | Affect daily life                                                                                                                                                    | Loss of basic self-care ability, or hospitalization             |
| Induration *, swelling * * # | 2.5 ~ < 5 cm in diameter or 6.25 ~ < 25 cm  in area not or slightly affecting daily life | 5 ~ < 10 cm in diameter or 25 ~ < 100 cm  in area or affecting daily life | Diameter ≥ 10 cm or area ≥ 100 cm  or ulceration or secondary infection or phlebitis or sterile abscess or wound drainage or seriously affect daily life | Abscess, exfoliative dermatitis, dermal or deep tissue necrosis |
| Rash *, flush * * #          | 2.5 ~ < 5 cm in diameter or 6.25 ~ < 25 cm  in area not or slightly affecting daily life | 5 ~ < 10 cm in diameter or 25 ~ < 100 cm  in area or affecting daily life | Diameter ≥ 10 cm or area ≥ 100 cm  or ulceration or secondary infection or phlebitis or sterile abscess or wound drainage or seriously affect daily life | Abscess, exfoliative dermatitis, dermal or deep tissue necrosis |
| Pruritus                     | Itching at the vaccination site was relieved by itself or within 48 hours after treatment            | Itching at the vaccination site did not relieve within 48 hours after treatment       | Affect daily life                                                                                                                                                    | NA                                                              |

Note:

\* In addition to measuring the diameter directly for grading evaluation, the progress and change of measurement results should also be recorded.

\*\* Maximum measured diameter or area shall be used.

# The evaluation and grading of induration and swelling, rash and redness should be based on the functional grading and actual measurement, with higher grading, being selected.

When judging severity, it can be judged as a next grade adverse event only when it meets the grading criteria of the previous one.

**CONFIDENTIAL**

**Table 4 Systemic Adverse Events Grading Table**

| Physical Sign                     | Grade 1                                                                                                         | Grade 2                                                                                         | Grade 3                                                                                                                                                        | Grade 4                                                                       |
|-----------------------------------|-----------------------------------------------------------------------------------------------------------------|-------------------------------------------------------------------------------------------------|----------------------------------------------------------------------------------------------------------------------------------------------------------------|-------------------------------------------------------------------------------|
| Fever * (axillary temperature °C) | 37.3 ~ < 38.0                                                                                                   | 38.0 ~ < 38.5                                                                                   | 38.5 ~ < 39.5                                                                                                                                                  | ≥ 39.5 for more than 3 days                                                   |
| Diarrhoea                         | Mild or transient, 3 ~ 4 times/day, abnormal faecal characteristics, or mild diarrhoea lasting less than 1 week | Moderate or persistent, 5 ~ 7 times/day, abnormal faecal characteristics, or diarrhoea > 1 week | > 7 times/day, abnormal faecal characteristics, hemorrhagic diarrhoea, orthostatic hypotension, and electrolyte imbalance, requiring intravenous infusion > 2L | Hypotensive shock, requiring hospitalization                                  |
| Constipation **                   | Need faecal softener and dietary adjustment                                                                     | Need laxative drugs                                                                             | Stubborn constipation requires manual dredging or enema                                                                                                        | Toxic megacolon or intestinal obstruction                                     |
| Dysphagia                         | Mild discomfort when swallowing                                                                                 | Restricted diet                                                                                 | Diet and conversation are very limited; can't eat solid food                                                                                                   | Can't eat liquid food; Need intravenous nutrition                             |
| Anorexia                          | Loss of appetite, but no reduction in food intake                                                               | Loss of appetite, food intake decreased, but body weight did not decrease significantly         | Loss of appetite and obvious weight loss                                                                                                                       | Need measures to intervene (e.g., gastric tube feeding, parenteral nutrition) |
| Vomiting                          | 1 ~ 2 times/24 hours without affecting activities                                                               | 3 ~ 5 times/24 hours or limited activity                                                        | > 6 times within 24 hours or intravenous rehydration is required                                                                                               | hospitalization or other nutrition due to hypotensive shock                   |
| Nausea                            | Transient (< 24 hours) or intermittent and normal food intake                                                   | Persistent nausea leads to reduced food intake (24 ~ 48 hours)                                  | Persistent nausea leads to almost no food intake (> 48 hours) or needs for intravenous rehydration                                                             | Life-Threatening                                                              |
| Myalgia (local)                   | not affect daily activities                                                                                     | Slightly affect daily activities                                                                | Severe myalgia seriously affects daily activities                                                                                                              | Emergency or hospitalization                                                  |

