### 4.3. Study Endpoint

**CONFIDENTIAL**

**Primary Endpoints:**

1. GMT and the 4-fold rise rate of anti-omicron neutralizing antibody 14 days after a single dose of the booster vaccine in adults  $\geq 18$  years of age.
2. The incidence and severity of any adverse reactions/events within 30 minutes after vaccination;
3. The incidence and severity of solicited adverse reactions/events within 0-7 days after vaccination;
4. The incidence and severity of unsolicited adverse reactions/events within 8-30 days after vaccination;
5. The incidence of SAE and AESI observed after vaccination and up to 12 months after full course of immunization.

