**CONFIDENTIAL**

\* Axillary temperature is usually used in China, tympanic temperature/temporal artery temperature = axillary temperature +0.5 °C. When persistent high fever occurs, the cause of high fever should be determined as soon as possible;

\*\* For constipation, attention should be paid to the changes before and after vaccination;

When judging severity, it can be judged as a next grade adverse event only when it meets the grading criteria of the previous one.

For clinical abnormalities not covered in the above table, the severity grading evaluation of adverse events should be carried out according to the following criteria.

| Grade 1                                                                                                     | Grade 2                                                                                                         | Grade 3                                                                                                             | Grade 4                                                                                                  | Grade 5 |
|-------------------------------------------------------------------------------------------------------------|-----------------------------------------------------------------------------------------------------------------|---------------------------------------------------------------------------------------------------------------------|----------------------------------------------------------------------------------------------------------|---------|
| Mild: Short-term (< 48h) or slight discomfort, which does not affect activities and does not need treatment | Moderate: Mild or moderate activity restriction, which may require medical treatment, no or only mild treatment | Severe: obvious activity
Restricted, need to see a doctor and receive treatment, and may need to be hospitalized | Critical: It may be life-threatening, severely limited in activities, and needs monitoring and treatment | Death   |

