### 7.7 Criteria for Suspension or Early Termination

- The number of participants with adverse reactions of severity Grade 3 or above exceeds 15% of the participants vaccinated in this subgroup;
- One case of Grade 4 adverse reaction related to vaccination or SUSAR;

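### Fever of 39.5 °C or more lasting 3 days or less fits no severity grade, and the step sentence under both grading tables conflicts with the bands and the note beside it

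*Protocol*

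**What the plan says.** All grading is in Protocol section 4.5.2.

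- **Fever row (Table 4 Systemic Adverse Events Grading Table).** By axillary temperature, Grade 1 is 37.3 to below 38.0 °C, Grade 2 is 38.0 to below 38.5 °C and Grade 3 is 38.5 to below 39.5 °C, none with a duration. Grade 4 is "≥ 39.5 for more than 3 days".
- **Vomiting row (same table).** Grade 2 is 3 to 5 times in 24 hours or limited activity. Grade 3 is "> 6 times within 24 hours or intravenous rehydration is required".
- **Step sentence (under both the local and the systemic table).** "When judging severity, it can be judged as a next grade adverse event only when it meets the grading criteria of the previous one".
- **# note (local table).** Induration, swelling, rash and redness "should be based on the functional grading and actual measurement, with higher grading, being selected".
- **Fallback scale (after the systemic table).** A generic Grade 1 to 5 scale, introduced by "For clinical abnormalities not covered in the above table".

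The grades are used in four places:

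- Section 4.3: severity is part of primary endpoints 2 to 4. Fever is a solicited event (section 4.5.1), so endpoint 3 is the main one: "The incidence and severity of solicited adverse reactions/events within 0-7 days after vaccination".
- Section 10.3.4: TEAEs of Grade 3 or higher are summarised by group, with Fisher's exact test for group differences.
- Section 7.3.1, item 5: Grade 3 or above calls for a face-to-face visit within 24 hours.
- Synopsis, sections 5.1.4 and 7.7: the trial is suspended if "The number of participants with adverse reactions of severity Grade 3 or above exceeds 15% of the participants vaccinated in this subgroup", or after one related Grade 4 reaction or one SUSAR.

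**The concern.** A severity scale must give every observed value one grade. Here the hole lies at the top of the temperature range: the upper limit of Grade 3 is closed, and the only cell above it also requires a duration. On the printed bands 39.0 °C for one day is Grade 3, while 40 °C for two days has no grade.

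The step sentence adds a second problem. If the criteria of the grade below must also be satisfied, a row with non-overlapping bands cannot progress, because a temperature in one band is by construction outside the band below it. Sites that meet these cases will have to improvise. The result feeds a primary safety endpoint, a between-group comparison, a visit trigger and a suspension count.

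**Working it through.** The protocol gives no figure to reproduce here, so the check applies its own criteria to test cases.

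**Step 1: fever under three readings.** Inputs are the four fever cells and the step sentence.

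- Reading A: bands as printed, no step sentence.
- Reading B: bands as printed, with the step sentence applied literally (grade g needs the criteria of grades 1 to g all met).
- Reading C: lower limits treated as cumulative thresholds (37.3, 38.0, 38.5, then 39.5 with more than 3 days), plus the step sentence.

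| Temperature, duration | A | B | C |
|---|---|---|---|
| 37.5 °C, 1 day | 1 | 1 | 1 |
| 38.2 °C, 1 day | 2 | none | 2 |
| 39.0 °C, 1 day | 3 | none | 3 |
| 39.5 °C, 1 day | none | none | 3 |
| 40 °C, 2 days | none | none | 3 |
| 40 °C, 3 days | none | none | 3 |
| 40 °C, 4 days | 4 | none | 4 |

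Reading A shows the gap. Reading B leaves every fever grade above 1 unreachable, so it cannot be what was intended. Reading C closes the gap, but the protocol does not state it and prints closed upper limits. A fourth possibility is the fallback scale, which grades by duration or degree of discomfort, activity restriction and need for treatment. The protocol does not say whether an uncovered value of a listed sign goes there.

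**Step 2: vomiting.** The frequency bands are 1 to 2, 3 to 5 and more than 6, so 6 is missing. Six episodes with limited activity reach Grade 2, and six with intravenous rehydration reach Grade 3, through the alternative criteria. Six with neither match no cell.

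**Step 3: the two notes side by side.** For induration, swelling, rash and redness, the # note takes the higher of the functional and measured grades. The step sentence that follows withholds a grade if the one below is not met. When the two dimensions disagree, the notes can give different answers.

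**Step 4: the suspension count.** Taking the subgroup as one group of 258 (section 4.2): 0.15 × 258 = 38.7, so 39 participants exceed 15%. The protocol gives no Grade 3 or higher rate and no share that would go ungraded. Both are assumed below, only to show how sensitive such a count is. With true rate p and ungraded share f, the probability of reaching the count is P(X ≥ 39), X ~ Binomial(258, p(1 − f)):

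| p | f = 0 | f = 10% | f = 25% |
|---|---|---|---|
| 12% | 0.08 | 0.02 | 0.001 |
| 15% | 0.51 | 0.25 | 0.03 |
| 18% | 0.90 | 0.71 | 0.25 |
| 20% | 0.98 | 0.90 | 0.51 |

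These are not estimates for this trial. In particular, nothing shows that fevers in the gap would make up 10% of Grade 3 or higher reactions.

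**The case against.** A reader might infer that severe reactions simply drop out of the safety evaluation. The documents do not support that, for these reasons:

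- Under the cumulative reading the gap fevers are Grade 3 and are counted.
- The fallback scale might take them. Its Grade 1 would apply only to an event that neither affects activity nor needs treatment, so a short high fever is not automatically Grade 1.
- An ungraded fever still counts in the incidence part of endpoint 3.
- The SUSAR limb of the suspension rule and SAE reporting (section 8.3) do not depend on grade.

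A reader might also infer that anaphylactic shock without the Grade 3 signs would trigger nothing, because the step sentence bars Grade 4. That goes too far: anaphylactic shock is a listed AESI (section 4.5.4), AESI incidence is primary endpoint 5, and the SAE and SUSAR routes remain open.

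Nor does a 12 cm swelling necessarily fail Grade 2, since that cell has an alternative criterion based on daily life. The same scale also applies to both blinded arms, and the immunogenicity endpoint is untouched.

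All of this limits the consequence. It does not remove the defect: the protocol does not choose among readings that give different grades for the same fever, and a two-day fever managed at home need not be an SAE, AESI or SUSAR, so the grade may be the only trigger that applies.

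**Conclusion.** The point holds as a gap and an internal contradiction in the grading rules. Fever of 39.5 °C or more for 3 days or less, and exactly 6 vomits in 24 hours meeting neither alternative criterion, match no cell. The step sentence cannot be applied literally to mutually exclusive bands and conflicts with the # note, and the scope of the fallback scale is undefined.

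Such reactions may therefore be ungraded or graded inconsistently wherever severity is used. How often this would happen cannot be computed: the protocol gives neither the frequency nor the duration of high fever. The conclusion rests only on the printed cells and notes. The guideline on which section 4.5.2 says the grading is based was not available.

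**What to change.** Before grading starts, reconcile five items in section 4.5.2: the fever row, the vomiting row, the step sentence under both tables, the # note and the sentence introducing the fallback scale. Every value of a listed sign should map to exactly one grade, with no gap. State whether an uncovered value of a listed sign goes to the generic scale. Remove or reword the step sentence so that it does not bar a grade whose own criteria are met. Program the eCRF to the same rules. Which grade applies to the gap values is for the sponsor to decide.

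One caution on wording: a blanket rule assigning the highest grade for which any single descriptor is met would misfire, because some rows repeat a descriptor across grades (abnormal stool in diarrhoea and reduced appetite in anorexia, each in Grades 1 to 3).

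The cost is wording in two tables and their notes, plus eCRF logic. No new data are needed. The downside is that the Grade 3 or higher count may be slightly higher.

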**CONFIDENTIAL**

|                                                   |                                                    |                                                                                                          |                                                                            |                                                                                                 |
|---------------------------------------------------|----------------------------------------------------|----------------------------------------------------------------------------------------------------------|----------------------------------------------------------------------------|-------------------------------------------------------------------------------------------------|
| Arthralgia                                        | Mild pain without hindering the function           | Moderate pain, need analgesics and/or pain interferes with function but does not affect daily activities | Severe pain, need for painkillers and/or pain affects daily activities     | Disabling pain                                                                                  |
| Headache                                          | not affect daily activities and not need treatment | Transient, slightly affect daily activities and may require treatment or intervention                    | Seriously affect daily activities and need treatment or intervention       | Intractable, requiring emergency or hospitalization                                             |
| Coughing                                          | Transient, without treatment                       | Persistent cough, effective treatment                                                                    | Paroxysmal cough, treatment uncontrollable                                 | Emergency or hospitalization                                                                    |
| Dyspnea                                           | Dyspnea during exercise                            | Dyspnea in normal activity                                                                               | Difficulty breathing at rest                                               | Difficulty breathing, needing oxygen therapy, hospitalization or assisted breathing             |
| Pruritus at non-vaccination site (No skin damage) | Slight itching not or slightly affects daily life  | affects daily life                                                                                       | Itching makes it impossible for daily life                                 | NA                                                                                              |
| Abnormal Skin Mucosa                              | Erythema/pruritis/colour                           | Diffuse rash/maculopapular rash/dryness/desquamation                                                     | Blister/exudation/desquamation/ulcer                                       | dermatitis involves mucosa, or erythema multiforme, or is suspected of Stevens-Johnson syndrome |
| Acute Allergic Reaction * *                       | Local urticaria (blister) without treatment        | Local urticaria, requiring treatment or mild angioedema, requiring no treatment                          | Extensive urticaria or angioedema requiring treatment or mild bronchospasm | Anaphylactic shock or life-threatening bronchospasm or laryngeal oedema                         |
| Tiredness/Fatigue                                 | Not affect daily activities                        | Affect daily activities                                                                                  | Seriously affect daily activities and cannot work                          | Emergency or hospitalization                                                                    |

Note:

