**CONFIDENTIAL**

respectively, the participants were followed-up by telephone and guided to observe the adverse events correctly and fill in the diary card.

3. On the 14th day after vaccination, the investigator reviews the filling of the diary card during this period and re-collect the diary card.
4. On the 8th -28th day after vaccination, the investigator uses telephone follow-up once a week, combined with an active report of the participants to monitor the safety.
5. When it is known that the participant has adverse reactions/events of Grade 3 or above, a face-to-face visit should take place within 24 hours.
6. SAEs and AESIs are observed from the first dose to 12 months after the full course of vaccination via monthly telephone follow-up calls and self-reports from the participants.
7. Participants should contact the doctors on informed consent form/diary card immediately if developed any COVID-19 like symptoms.

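### The Abnormal Skin Mucosa row of the systemic grading table lists desquamation under both Grade 2 and Grade 3, with nothing to tell the two entries apart

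*Protocol*

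**What the plan says.** Section 4.5.2 fixes the severity criteria in the protocol itself and bases them on a named national guideline on adverse event grading in preventive vaccine trials. Table 4 of that section covers systemic events. Its Abnormal Skin Mucosa row contains:

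- Grade 1: "Erythema/pruritis/colour"
- Grade 2: "Diffuse rash/maculopapular rash/dryness/desquamation"
- Grade 3: "Blister/exudation/desquamation/ulcer"

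Abnormal skin mucosa is one of the systemic terms collected in days 0-7 (section 4.5.1). The severity of solicited events in that period is a primary endpoint (section 4.3).

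Two notes bear on the choice between grades. The note under Table 4, repeated under Table 3, allows the next grade only if the criteria of the grade below are met. The hash note under Table 3 says that grading of induration, swelling, rash and redness "should be based on the functional grading and actual measurement, with higher grading, being selected".

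The line between Grade 2 and Grade 3 is used elsewhere. Section 7.3.1, item 5, says that for "adverse reactions/events of Grade 3 or above, a face-to-face visit should take place within 24 hours". Section 10.3.4 summarises Grade 3 or above TEAEs, and the vaccine-related ones among them, by group with a Fisher exact test. The suspension criteria (Synopsis, sections 5.1.4 and 7.7) count adverse reactions of Grade 3 or above against 15% of those vaccinated in the subgroup.

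**The concern.** A severity table should give one grade for one presentation. Here an investigator who sees desquamation and nothing else finds it named in two adjacent cells of the same row. Two investigators can both follow the table and record different grades.

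The overlap lies on the Grade 2/3 line, which is the one the protocol acts on. For the individual participant, the recorded grade decides whether the 24-hour visit is required. For the analysis, it decides whether the event enters the Grade 3 or above comparison, and it feeds the severity part of a primary safety endpoint. Because grading is blinded, the expected result is misclassification noise and not a systematic difference between groups. A comparison that may rest on few events is nevertheless sensitive to single reclassifications.

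**Working it through.** There is no stated figure to reproduce. The check is a reading of the cells and of every rule that could separate them, followed by a short scale calculation.

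**1. The two cells.** Both are intact. Grade 2 lists desquamation after dryness. Grade 3 lists it between exudation and ulcer. Neither entry carries an extent, a depth, a type, a need for treatment or an effect on daily life. The overlap is confirmed.

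**2. The next-grade note under Table 4.** It sets a necessary condition: Grade 3 requires that the Grade 2 criteria are met. Desquamation meets the Grade 2 cell by name, so the condition is satisfied. It also meets the Grade 3 cell by name. The note therefore blocks nothing. If satisfying it were read as enough for promotion, every desquamation would become Grade 3 and the Grade 2 entry would have no function.

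**3. The hash note.** It is attached to Table 3 and names four local signs. Desquamation is not among them, and Table 4 has no counterpart.

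**4. The generic five-grade scale below Table 4.** It applies to abnormalities that the tables leave out. Desquamation is covered twice, so the scale is not reached.

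**5. Scale.** Inputs: 258 participants per booster group (section 4.2) and the 15% threshold (section 5.1.4). Assumption: the subgroup in the suspension rule means a booster group.

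- Threshold: 0.15 × 258 = 38.7, so more than 15% means at least 39 participants.
- One reclassified participant: 1/258 = 0.39 percentage points of a group's Grade 3 or above incidence.

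The protocol gives no rate for skin events in general or for desquamation, so the number of participants affected cannot be estimated from it.

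**The case against.** The strongest reply is that this is one duplicated word in one row, perhaps carried over from the cited guideline or lost in translation, and that clinicians will read the neighbouring words as context: dry scaling in Grade 2, weeping lesions in Grade 3. The origin of the duplicate cannot be settled without the guideline, and that part stands. The dry-versus-weeping reading is plausible, but the protocol does not state it, so graders would be supplying the rule themselves.

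It is also fair to say that Table 4 is not without rules, since it has its own next-grade note. That note exists, but it does not separate these two entries.

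A reader might infer that the whole set of skin rows overlaps. The protocol does not support this:

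- **Itching.** It appears in Grade 1 of the skin row, and it also has its own row, graded by effect on daily life up to "Itching makes it impossible for daily life". That row is confined to itching without skin damage, and section 4.5.1 repeats the limit. The rows are kept apart.
- **Blister.** It is a Grade 3 sign in the skin row and appears in Grade 1 of the Acute Allergic Reaction row as "Local urticaria (blister) without treatment". There the bracket only explains urticaria, and section 4.5.1 lists the two rows as separate solicited terms. This is not one sign in two grades of one term. What remains is narrower: no rule says which row governs a blistering or urticarial lesion.

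**Conclusion.** The point holds for desquamation. Table 4 gives two grades for the same sign in the same row, and nothing in the protocol resolves them. The consequence is concrete for the individual participant, because the 24-hour visit both is and is not called for. It is also concrete for entry into the Grade 3 or above summaries.

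The size is small. Each reclassified participant moves a group's Grade 3 or above incidence by about 0.39 percentage points. How many participants that would be is unknown, and any total effect would be an assumption and not a result.

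A reader might infer that the suspension rule is at risk. With a threshold of at least 39 of 258 (taking the subgroup as a booster group), a handful of desquamation events is unlikely to decide it. Nor is there ground to expect bias between groups while grading is blinded. This is a minor correction, worth making because it is cheap and falls on a line that the protocol acts on.

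**What to change.** Reconcile the two desquamation entries in the Abnormal Skin Mucosa row with the grading guideline that section 4.5.2 cites. Either outcome is acceptable statistically: each entry carries a qualifier that distinguishes it, or the sign stands in one grade only. If the guideline contains the same duplicate, the protocol needs a stated rule of its own. Which grade applies is for the sponsor to decide. Any such rule should be worded so that it works together with the existing next-grade note.

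As a secondary clarification, state which row governs blistering or urticarial lesions, so that the term is chosen before the grade.

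Carry both changes into the eCRF grading help. The cost is the wording of one table row, one sentence in its notes and the matching help text. No visits, samples or data items are added, and the sample size is unaffected.
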